## 6.3 Study procedures

### 6.3.1 Screening

#### *Anthropometrics*

Body weight will be measured using a digital balance with subjects in underwear, in the fasted state and after voiding their bladder. Height will be measured by a wall-mounted stadiometer. BMI will be calculated as body weight (kg) divided by height (m) squared. Waist and hip circumference will be determined in standing position by a tape measure. Waist circumference will be measured at the smallest circumference between rib cage and iliac crest, and hip circumference at the level of the spina iliaca anterior superior. Accordingly, waist-to-hip ratio (WHR) will be calculated by dividing waist circumference by hip circumference. Both waist circumference and WHR will be used to define different patterns of body fat distribution.

#### *Eating behaviour*

Eating behavior will be analyzed using a Dutch translation of the Three Factor Eating Questionnaire (TFEQ), which measures the three factors (F) involved in eating behavior, namely 'cognitive restraint of eating' (F1), 'disinhibition of restraint' (F2) and 'hunger' (F3) (28). Dietary restraint reflects the extent to which individuals attempt to cognitively control their food intake. Disinhibition reflects the extent to which release from the cognitive suppression of eating occurs in response to the presence of palatable food or other disinhibiting stimuli, such as emotional distress. Hunger refers to the subjective feeling of hunger. Based upon the median in the population from south of the Netherlands, dietary restraint was defined by TFEQ F1 scores  $\geq 9$ . F1 scores  $< 9$  indicated dietary unrestraint (14). High disinhibition was defined by TFEQ F2 scores  $\geq 5$ , and F2 scores  $< 5$  represented low disinhibition. Completing the questionnaire will take about 3 minutes.

#### *Anxiety*

The STAI state questionnaire refers to the transitory emotional response involving unpleasant feelings of tension and apprehensive thoughts. The STAI scale is composed of 20 questions rated on a four-point scale, ranging from 'much like this' to 'much unlike this' and requires that subjects describe how they feel generally (Trait Anxiety Inventory scale). The questionnaire can score a maximum of 80, whereby increased scores are associated with an increase in anxiety (43). Completing both questionnaires will take about 3 minutes.

#### *Physical activity*

Habitual physical activity is evaluated using a Dutch translation of the Baecke questionnaire. This questionnaire consists of three subscales: work activity, sports activity and non-sports leisure activity (29).

#### *Glomerular Filtration Rate*

The glomerular filtration rate will be estimated using the MDRD study equation. The MDRD equation uses four variables (serum creatinin, age, race and gender) to estimate the glomerular filtration rate (44, 45). To determine serum creatinin concentrations, a blood sample of 10ml will be collected via vena puncture in the antecubital vein.

### **6.3.2 Intervention**

#### *Energy expenditure*

Oxygen consumption and carbon dioxide production will be measured in the respiration chamber. The respiration chamber is a 14m^3 hotel room, furnished with a bed, chair, computer, television, radio, dvd-player, telephone, intercom, sink and toilet. The room is ventilated with fresh air at a rate of 70-80 l/min. The ventilation rate is measured with a dry

gas meter. The concentrations of oxygen and carbon dioxide will be measured using a paramagnetic O2 analyzer and an infrared CO2 analyzer. During each 15-min period six samples of outgoing air for each chamber, and one sample of fresh air, zero gas, and calibration gas will be measured. The gas samples to be measured will be selected by a computer that also stores and processes the data (46).

24-h energy expenditure consists of sleeping metabolic rate (SMR), diet-induced energy expenditure (DEE), and activity-induced energy expenditure (AEE). 24-h energy expenditure and 24-h respiratory quotient (RQ) will be calculated using the formula of Brouwer (39). Physical activity is monitored using a radar system working on the Doppler principle. SMR is defined as the lowest mean energy expenditure measured over three consecutive hours between 00:00h and 07:00h. DEE will be calculated by plotting energy expenditure against radar output, both averaged over 30-min periods. The intercept of the regression line at the lowest radar output represents the energy expenditure in the inactive state (Resting Metabolic Rate; RMR), consisting of SMR and DEE (47). DEE will be determined by subtracting SMR from RMR. Activity-induced energy expenditure will be determined by subtracting RMR from 24-h energy expenditure. The Physical Activity Level (PAL) will be calculated by dividing 24-h energy expenditure by SMR.

#### *Substrate oxidation*

Carbohydrate, fat and protein oxidation will be calculated using oxygen consumption, carbon dioxide production and urinary nitrogen excretion, with the formula of Brouwer (39). Urine will be collected during each 48h stay in the respiration chamber. Samples will be collected in containers with 10ml diluted HCl to prevent nitrogen loss through evaporation. The subjects will be told, before entering the respiration chamber, to handle the urine containers with the most caution because of the presence of the diluted HCl. Volume and nitrogen concentration will be measured, the latter using a nitrogen analyser.

#### *Sleep*

During each stay in the respiration chamber, sleep will be monitored continuously via polysomnography. The subject is only allowed to sleep on the times stated by the investigator, so daytime naps and sleeping is not allowed, and will be controlled via the polysomnographic measurements. Polysomnography typically consists of 4 measurements: EEG, EMG, EOG and ECG. To measure brain activity (EEG) 6 electrodes are placed on the head. These electrodes provide a readout of the brain activity that can be "scored" into different stages of sleep (N1, N2, N3 which combined are referred to as NREM sleep, and rapid eye movement sleep or REM, and Wakefulness). In addition, to determine if sleep occurs and especially to determine when REM sleep occurs, 2 electrodes on the chin and 2

electrodes on the eyes are necessary to measure muscle activity (EMG) and eye movements (EOG). Finally, 2 additional electrodes are placed on the chest to monitor heart rate and cardiac function (ECG). The combination of these data will make it possible to determine sleep duration and sleep quality. Sleep quality represents the amount of minutes in which the subject is in sleep stage N3 plus REM sleep divided by the total duration of sleep.

Subjective feelings of sleep will be assessed before each meal in the respiration chamber using 100 mm VAS with questions on subjective feelings of napping, physical exhaustion, alertness, sleepiness and how satisfying the sleep was. Opposing extremes of each feeling are described at either end of the 100-mm horizontal line, and subjects mark the line to indicate how they feel at that moment. An example of this questionnaire is attached to the protocol.

#### *Body composition*

Subjects' body composition will be calculated from body volume and total body water using the combined equation of Siri (40). Body volume is measured with a BodPod. Total body water is measured with Deuterium dilution according to the Maastricht protocol (41). Subjects drink a Deuterium dilution (about 70 g with an enrichment of 5 atom% excess  $^2\text{H}$ ) in the evening prior to the measurements after the collection of a baseline urine sample. The next morning after a 10-hour equilibration period, where subjects are not allowed to eat or drink, a second urine sample is collected.

#### *Magnetic resonance imaging (MRI) and Magnetic resonance Spectroscopy (MRS)*

MRI and MRS are non-invasive and non-irradiant imaging techniques, which will be used to determine abdominal fat and muscle mass of the upper part of the lower limbs (MRI), muscle and liver fat (MRS).

An MRI (magnetic resonance imaging) scan will be performed with a whole body scanner (Intera, Philips Medical Systems) to quantify fat distribution and regional muscle mass. A single-slice breath-hold turbo spin-echo (TSE) sequence (turbo factor 5, echo time TE 12 ms, TR 200 ms, slice thickness 10 mm, field-of-view (FOV) 420-450 mm, total measurement time 11 s) is modified to suppress the water signal so that the images contain mainly the fat signal. The breath-hold technique is used to avoid any motion artifacts (ghosting due to the movement of subcutaneous fat regions with high signal intensity), which would cause difficulties during the data segmentation. This technique is performed to measure fat content in the subcutaneous abdominal and visceral fat. Detailed measurement of abdominal fat was described by Tintera et al. (48). Transversal images will be made from the upper part of the lower limbs. Muscle mass will be expressed as volumes (cubic centimeters), derived by using tissue area measurements from multiple images. MRI is a safe procedure with no

ionizing radiation and no known risks as long as the exclusion criteria (no electronic implants, no pacemakers, no metal fragments in the eyes, skin or body) are not met.

Image guided localized single voxel H-MRS will be performed in the m.vastus lateralis at the start and after 12 weeks. The measurements are performed on a whole body scanner (Intera, Philips Medical System, Best, the Netherlands) with a flexible surface coil wrapped around the upper leg. This technique is performed to measure fat content in the muscle (intramyocellular lipid; IMCL). Detailed intramyocellular lipid measurement is described by Schrauwen-Hinderling et al. (49). While fat content in the liver will be determined using an MRS protocol as described by Stefan et al. (50).

#### *Blood samples*

Plasma concentrations of glucose, insulin and which will be measured before each breakfast in the respiration chamber by drawing one blood sample of 10ml from the antecubital vein of the contra-lateral arm using venapuncture. Within this study, a total of 174 mL venous blood will be collected from each subject, i.e. 3 x 10 mL for the glucose and insulin and 144 mL (18x8mL) during the additional test day. Aliquots of plasma will be frozen in liquid nitrogen and stored at -80°C until analysis of glucose (Uni Kit III, La Roche, Basel, Switzerland) and insulin by radio immunoassay (Linco, Human Insulin RIA kit). Phenylalanine, leucine and tyrosine enrichment in plasma samples and in the muscle free amino acid pool will be measured using gas chromatography-mass spectrometry (Agilent G1530N/G2589A, Little Falls, USA), while the phenylalanine enrichment in muscle proteins will be measured with GC-combustion IRMS (Finnigan MAT 252, Bremen, Germany) (51). In all plasma samples glucose, insulin and amino acid concentrations and amino acid tracer/tracee ratio's will be measured.

#### *Physical activity.*

Habitual physical activity will be measured using a triaxial accelerometer for movement registration (TracmorD; DirectLife, Philips new wellness solutions, Amsterdam, The Netherlands) sensitive to a wide range of body movements. The accelerometer has been validated with doubly labelled water, the gold standard for measuring energy expenditure in daily life (52). The accelerometer will be worn under free-living conditions one week before the baseline measurement and one week before the final measurement. Subjects will be instructed to wear the TracmorD from the moment they wake up in the morning until they go back to bed at night. The TracmorD is only a small device that will be worn on a belt around the waist. To verify whether subjects live up to this instruction, waking hours and clock times of wearing the TracmorD have to be noted.

*Mood, feelings of hunger and satiety*

Appetite and mood profiles will be measured hourly and before and after each meal, by visual analogue scales (VAS) and by Profile of Mood States (POMS) and State Trait Anxiety Index (STAI) questionnaires (42, 43). Examples of these questionnaires are attached to the protocol.

Aspects of appetite will be assessed using 100 mm VAS with questions about feelings of hunger, satiety, thirst, and desire to eat. Opposing extremes of each feeling are described at either end of the 100-mm horizontal line, and subjects mark the line to indicate how they feel at that moment.

The POMS questionnaire contains 70 adjectives that are rated on a five-point scale, anchored by “much like this” to “much unlike this” and is divided into five subscales (depression, tension, confusion, fatigue and anger), each scoring a maximum of 35. An increase in POMS scores is associated with a worsening in mood, except in the case of “vigor”.

The STAI state questionnaire refers to the transitory emotional response involving unpleasant feelings of tension and apprehensive thoughts. The STAI scale is composed of 20 questions rated on a four-point scale, ranging from “much like this,” to “much unlike this” and requires that subjects describe how they feel generally, on the anxiety-trait scale, and how they feel at a specific moment, on the anxiety-state scale. The questionnaire can score a maximum of 80 and an increase in STAI state scores is associated with an increase in anxiety.

Filling out the questionnaires will take about a minute per questionnaire, in total 3 minutes.

*Melatonin and serotonin*

Urine will be collected during each 48h stay in the respiration chamber to measure 6-sulfatoxymelatonin (urinary metabolite of melatonin) and 5-hydroxy-3-indole acetic acid (urinary metabolite of serotonin). An enzyme-linked immunosorbent assay will be used to determine urinary 6-sulfatoxymelatonin and 5-hydroxy-3-indole acetic acid levels.

*Energy intake*

Our subjects are in overall energy balance, as they are weight stable for at least three months and not currently on a diet. Two days before the first stay in the respiration chamber and during all their stays in the respiration chambers, subjects will be fed in energy balance. Calculations will be based upon average daily energy requirements (DER). The daily energy requirement for the two days before the experiment will be estimated as 1.75 times the Basal Metabolic Rate (BMR) (53). BMR will be calculated with the equation of Harris and Benedict (54). The energy requirement in the respiration chamber will be calculated as 1.4 times the

measured sleeping metabolic rate (SMR) of the first night. The selected activity index is based on results of a study in which physical activity was determined in confined conditions (a respiration chamber) resulting in a mean PAL of 1.4 (calculated as 24-h energy expenditure/SMR) (55). Daily energy intake will be divided over three meals: breakfast 20%, lunch 40% and dinner 40%. Breakfast will be given at 08:30 hours, lunch at 13:30 hours and dinner at 18:30 hours. During the first stay in the respiration chamber, the macronutrient composition of the diet will be 15/50/35 En% (Protein/ Carbohydrate/Fat). During the second and third stay in the respiration chamber, the macronutrient composition of the diet will be 5/60/35 En% for the one group and 30/35/35 En% for the other group. The diets consist of normal food products, which are commercially available in normal Dutch supermarkets. The protein supplements for the diet with 30 En% of protein and the carbohydrate supplements for the diet with 5 En% of protein are commercially available. A qualified dietician will freshly prepare the meals in a qualified research kitchen, just before they are offered to the subjects.

The use of polysomnography and MRI are exclusively intended for scientific purposes. The researchers are not trained to make a clinical diagnosis of the results. However, it could be that by coincidence a possible deviation may be found. In this case, a medical expert will look at the data and when necessary the subject will be referred to a medical specialist.

#### *(Muscle) protein synthesis*

An outline of the study protocol of a test day is shown in **Figure 2**. At 8.00 am, following an overnight fast, subjects will arrive at the laboratory by car or public transportation. A Teflon catheter (Baxter BV, Utrecht, the Netherlands) will be inserted into an antecubital vein for intravenous stable isotope infusion. A second Teflon catheter will be inserted in a heated dorsal hand vein of the contra lateral arm and placed in a hot-box (60°C) for arterialized blood sampling (56). Following basal blood collection ( $t=-150$  min), the plasma phenylalanine and tyrosine pools will be primed with a single intravenous dose of both tracers, after which continuous tracer infusion will be started that will be administered until the end of the test day (8½ h). After resting in a supine position for 90 min, a second arterialized blood sample will be drawn and a muscle biopsy will be collected from the *vastus lateralis* muscle ( $t=-120$  min). Arterialized blood samples (8 mL) will be collected at  $t=-90$ ,  $-60$ ,  $-30$ , and 0 min during the postabsorptive (fasted) period with a second muscle biopsy taken from the same at  $t=0$  min, marking the end of the postabsorptive period. Subjects will then receive the test-drink containing 20 g intrinsically labelled casein. Arterialized blood samples (8 mL) will be collected at  $t=15$ , 30, 45, 60, 90 and 120 min during the postprandial (fed) period. The third muscle biopsy is then taken from a new incision, 5 cm distal from the first incision, from the same leg at  $t=120$  min. Subsequently, arterialized blood samples (8 mL) will be collected at

t=150, 180, 210, 240, 270, 300 min. Finally, at 300 min a fourth muscle biopsy will be taken from the same incision as the last biopsy. In total, four muscle biopsies will be taken through two separate incisions. At the end of the test day, subjects will receive a standard lunch before they go home.

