### 5.2.1 Intravenous tracer infusion

The stable isotopic tracers (L-[H5]-phenylalanine, [H2]-tyrosine and L-[1-C]-leucine) will be purchased from Cambridge Isotopes (Andover, USA) and dissolved in 0.9% saline before infusion. Tracer solutions for intravenous administration will be prepared by Basic Pharma following GMP-standards (Appendix D2.3). Continuous intravenous infusion during the entire period of the test day (8½ h, 0.05 µmol/kg/min L-[H5]-phenylalanine, 0.02 µmol/kg/min [H2]-tyrosine, 0.12 µmol/kg/min L-[1-C]-leucine) of the labeled stable isotopes will be performed using a calibrated IVAC 560 pump (San Diego, USA). The phenylalanine, tyrosine and leucine pools will be primed, such that whole body steady state labeling of the amino acids will be achieved within 90 min. Using these tracers in whole body phenylalanine kinetics can be calculated using established tracer models (31), which have been applied in multiple previous studies within our group (24-26, 32-38).

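### The test-day tracer schedule contradicts itself: a start at t=-150 min fits neither the 90-min rest before the first biopsy nor the 8½-h infusion, and fasted FSR could be biased if the printed times are followed

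*Protocol*

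**What the plan says.** Section 6.3.2, (Muscle) protein synthesis, gives the test day as a running clock with t=0 at the casein drink. Basal blood is drawn at t=-150 min. Then "the plasma phenylalanine and tyrosine pools will be primed with a single intravenous dose of both tracers", and "continuous tracer infusion will be started that will be administered until the end of the test day (8½ h"). The next step is: "After resting in a supine position for 90 min, a second arterialized blood sample will be drawn and a muscle biopsy will be collected"; this step is labelled t=-120 min. Blood follows at -90, -60, -30 and 0, with the second biopsy at 0. The drink is then given, and the last blood sample and the fourth biopsy are at t=300.

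Section 5.2.1 gives the same infusion length: "Continuous intravenous infusion during the entire period of the test day (8½ h"). On priming it says "The phenylalanine, tyrosine and leucine pools will be primed". It gives the intended result of that priming as follows: "such that whole body steady state labeling of the amino acids will be achieved within 90 min".

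Section 6.1.2 lists FSR among the secondary endpoints, with plasma and muscle enrichment of both phenylalanine and leucine among its inputs. Section 3 makes the test day optional.

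**The concern.** The start time, the rest period, the first-biopsy time and the infusion length cannot all be true, so staff cannot carry out the paragraph as printed. Which value they give way on matters for the fasted FSR, which rests on the interval between the biopsies at -120 and 0.

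A tracer-based FSR relates the gain in protein-bound enrichment between two biopsies to the precursor enrichment over that interval. If precursor enrichment is still rising at the first biopsy, a plateau value does not describe the whole interval. On the printed clock the fed interval begins 150 min into infusion (0 - (-150)), well past the protocol's own 90-min mark. Any such error would therefore fall on the fasted value alone and would distort the fasted-versus-fed comparison. The introduction states separate expectations for basal and post-prandial synthesis, so that comparison is of interest.

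The leucine discrepancy bears on the same endpoint. Section 5.2.1 ties its 90-min statement to priming all three pools, while section 6.3.2 primes two.

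**Working it through.** **Inputs.**
- Basal blood, followed by prime and infusion start: t=-150 (section 6.3.2)
- Rest before the first biopsy: 90 min (section 6.3.2)
- First biopsy: t=-120 (section 6.3.2)
- Infusion length: 8½ h = 8.5 × 60 = 510 min (sections 5.2.1 and 6.3.2)
- Last timed procedure: t=300 (section 6.3.2)
- Steady state: within 90 min (section 5.2.1)
- Test-day blood: 18 × 8 mL = 144 mL (section 6.3.2, Blood samples)

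**Step 1: start at -150, as printed.**
- Infusion start to first biopsy: -120 - (-150) = 30 min, against a stated 90 min. Infusion follows the basal sample, so 30 min is the most it can be.
- Infusion start to last procedure: 300 - (-150) = 450 min = 7½ h, against a stated 8½ h. The gap is 510 - 450 = 60 min.
- Resting 90 min from -150 puts the biopsy at -150 + 90 = -60, after the -90 sample that the text lists later.
- Infusing 510 min from -150 ends at -150 + 510 = 360, where nothing is scheduled.

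**Step 2: count back from the other values.**
- From the first biopsy: -120 - 90 = -210.
- From the last procedure: 300 - 510 = -210.

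The 90-min rest, the -120 biopsy and the 8½ h agree with one another. Only -150 is out of line, by 60 min on both counts.

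**Step 3: does the blood count settle it?** There are six samples up to t=0 (basal, -120, -90, -60, -30, 0), six from 15 to 120 and six from 150 to 300. That is 18, and 18 × 8 = 144 mL. The protocol's figure reproduces, but it is the same whether the basal sample is at -150 or -210, so it does not decide the start time.

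**Step 4: position against steady state.** With a start at -150, the 90-min mark falls at -60. The biopsy at -120 precedes it, as does the stretch from -120 to -60, which is 60 of the 120 fasted minutes. With a start at -210, the 90-min mark falls at -120, exactly at the biopsy.

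**Step 5: illustration of size, on an assumption the protocol does not make.** Suppose precursor enrichment rises as 1 - exp(-kt) and reaches a fraction f of plateau at 90 min, so k = -ln(1 - f)/90. At 30 min the fraction is 1 - (1 - f)^(1/3). The mean over infusion minutes 30 to 150 is 1 - [exp(-30k) - exp(-150k)]/(120k).

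| f at 90 min | Fraction at 30 min | Mean over fasted window, start -150 | Mean over fasted window, start -210 (minutes 90 to 210) |
|---|---|---|---|
| 0.95 | 0.63 | 0.91 | 0.99 |
| 0.99 | 0.78 | 0.96 | 1.00 |

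Using a plateau value as precursor with a start at -150 would then understate fasted FSR by roughly 4 to 9%. Using the mean of the serial fasted samples would remove most of that.

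**Step 6: priming.** Section 5.2.1 names phenylalanine, tyrosine and leucine. Section 6.3.2 names phenylalanine and tyrosine and speaks of both tracers. Leucine is infused and measured, so the two lists do not match.

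**The case against.** The strongest reply is that this is one misprinted label. Three values agree on -210, section 6.3.2 refers to Figure 2 for the outline of the day, and staff may already be working from a correct figure. On that reading the first biopsy falls at the 90-min mark and nothing is biased. This stands as a limit on the consequence. It does not remove the contradiction in the text, and Figure 2 is not visible in the text at hand, so it cannot be used to settle the matter.

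Second, within 90 min is an upper bound. A primed infusion may reach steady state sooner, so the claim that half the fasted window precedes it is a worst case. This stands.

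Third, the 7½-h result takes t=300 as the end of the test day. The protocol says the infusion runs to the end of the day without giving that a clock time. This also stands, but no later procedure is timed, and the 30-versus-90-min conflict does not depend on it.

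A reader might go further and infer that a 90-min rest from -150 shortens the fasted interval to 60 min, so that dividing by 120 would halve the FSR. The documents do not support this. It needs a biopsy at -60, out of order with the listed -90 sample, and a calculation on nominal times that the protocol nowhere states.

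Finally, the leucine mismatch is a separate inconsistency. It needs the same reconciliation but adds no weight to the timing argument.

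**Conclusion.** The schedule contradicts itself and cannot be executed as printed. Start at -150 conflicts with the 90-min rest by 60 min and, taking t=300 as the end of the day, with the 8½-h infusion by the same 60 min.

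The effect on results is conditional. If the printed -150 and -120 are followed, the first biopsy can fall before steady state and the fasted FSR could be biased. The protocol gives no figure for the size, and the 4 to 9% above is an illustration that rests on an assumed rise curve and on using a plateau precursor value. If infusion starts at -210, this problem does not arise. It would be wrong to read the text as showing that fasted FSR is biased.

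The point affects a secondary endpoint from a voluntary test day. Energy expenditure, substrate oxidation and sleep are untouched. It is worth correcting because it governs timed biopsies that cannot be repeated, but it does not threaten the trial's main conclusions.

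**What to change.** Before the first test day, the sponsor should reconcile five items across section 5.2.1, section 6.3.2 and Figure 2:
- the infusion start time
- the rest period
- the time of the first biopsy
- the infusion length
- the list of primed pools, including whether leucine is primed

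Which values are right is for the sponsor to determine; the documents show only that they do not agree. The reconciled text should make clear how the first biopsy sits relative to the protocol's own 90-min statement.

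The sponsor should also confirm the plasma enrichment plateau over the fasted window, using the samples already scheduled from the first biopsy to t=0.

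The cost is the correction of one schedule paragraph, agreement with the tracer section and the figure, and a check on data already planned. No extra samples or procedures are needed.

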To assess dietary protein intake and thus compliance to the diet, subjects will complete 24-hour urine collections at the start, during their stays in the respiration chamber and at week 11. One week before the baseline measurement and at week 11 an accelerometer will be worn to measure habitual physical activity.

During the screening, after 6 weeks and after 12 weeks of high protein diet the glomerular filtration rate (GFR) will be estimated using the Modification of Diet in Renal Disease (MDRD) study equation (for detail see section 6.3).

After the final measurement in the respiration chamber the subjects are invited for a final test day in which (muscle) protein synthesis will be measured. This additional test day is not compulsory and subjects that do not want to participate can still take part in the rest of the study.

During the test day, subjects will receive a test-drink containing 20 g intrinsically labelled casein to be able to measure the effect of protein ingestion on muscle protein synthesis. This allows us to determine the true incorporation of amino acids from the ingested, intact casein into the muscle, taken into account the influence of digestion and absorption processes of a whole protein (24-27). Intrinsically labelled milk proteins were derived from milk that has been collected from cows that were infused with L-[1-C] phenylalanine (27). This procedure has been successfully used in human intervention studies by the research group of [name]. [name] (MEC 06-3-064, MEC 07-3-086, MEC 09-3-078.3, MEC 10-3-080), which has already resulted in multiple publications (24-27). Subsequently, plasma and muscle samples will be collected. Together with the use of an intravenous L-[ring-H5]phenylalanine, L-[1-C]-leucine and L-[ring-H2]tyrosine infusion, the digestion and absorption kinetics of the ingested protein, whole body protein balance and the fractional synthetic rate (FSR) of mixed muscle protein in the fasted and fed state in an *in vivo* human setting will be assessed.

[figure not shown]

**Figure 2:** time schedule of the additional test day.

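### Protocol 6.3.2, muscle protein synthesis test day: a start at t=-150 min contradicts both the 90-minute rest before the t=-120 biopsy and the 8½-hour infusion; t=-210 fits both

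*Protocol*

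**What the plan says.** Protocol 6.3.2, (Muscle) protein synthesis, sets out the test day in sequence:

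- Basal sample and prime: "Following basal blood collection ( $t=-150$ min), the plasma phenylalanine and tyrosine pools will be primed with a single intravenous dose of both tracers".
- Infusion, begun after the prime: "continuous tracer infusion will be started that will be administered until the end of the test day (8½ h").
- Rest and first biopsy: "After resting in a supine position for 90 min, a second arterialized blood sample will be drawn and a muscle biopsy will be collected". The time attached to this step is "muscle biopsy will be collected from the *vastus lateralis* muscle ( $t=-120$ min").
- Further samples and a second biopsy up to t=0, then the casein drink, then samples and two more biopsies, the last at t=300. Only lunch follows.

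Section 5.2.1 repeats the infusion length, "Continuous intravenous infusion during the entire period of the test day (8½ h", and says the pools are primed so that "whole body steady state labeling of the amino acids will be achieved within 90 min". The Blood samples part of 6.3.2 budgets "144 mL (18x8mL) during the additional test day". Section 3 says of the day as a whole: "This additional test day is not compulsory".

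**The concern.** The time label on the start of the tracer protocol conflicts with two durations that the protocol states separately: the rest before the first biopsy and the length of the infusion. All three cannot hold together, so the day cannot be run as printed.

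The interval from prime to first biopsy matters because that biopsy opens the fasted window over which post-absorptive FSR is measured; the biopsy at t=0 closes it. The 90-minute rest matches the time the protocol allows for reaching steady-state labelling. Someone who follows the clock labels instead would biopsy after 30 minutes, possibly before steady state, and the fasted FSR could be biased. The length of an intravenous infusion in volunteers should also not be open to two readings.

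**Working it through.** **Inputs**

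| Item | Value | Source in Protocol |
|---|---|---|
| Basal sample, then prime and infusion start | t=-150 min | 6.3.2, (Muscle) protein synthesis |
| Rest before second sample and first biopsy | 90 min | same |
| First biopsy | t=-120 min | same |
| Last sample and fourth biopsy | t=300 min | same |
| Infusion length | 8½ h = 510 min | same, and 5.2.1 |
| Time to steady-state labelling | within 90 min | 5.2.1 |
| Test-day blood | 18 × 8 mL = 144 mL | 6.3.2, Blood samples |

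**1. Do the printed labels reproduce the stated durations?**

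- Start to first biopsy: -120 - (-150) = 30 min. Stated: 90 min. Shortfall: 90 - 30 = 60 min.
- Start to last procedure: 300 - (-150) = 450 min = 7½ h. Stated: 510 min. Shortfall: 510 - 450 = 60 min.

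Neither duration is reproduced, and both miss by the same 60 minutes.

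**2. What start time do the durations imply?**

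- From the rest: -120 - 90 = -210.
- From the infusion: 300 - 510 = -210.

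Two separately stated durations give the same start.

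**3. Could something other than t=-150 be the slip?**

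- *Keep t=-150 and the 90-minute rest.* The first biopsy moves to -150 + 90 = -60, against the printed -120, and the infusion to t=300 is still 7½ h.
- *Keep t=-150 and the 8½ h.* The infusion ends at -150 + 510 = 360, which is 60 minutes after the last listed procedure, and the rest is still 30 minutes by the labels.
- *Keep both labels and read the rest as 30 minutes.* The 8½ h remains unexplained, and the first biopsy falls before the 90 minutes allowed for steady state.

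**4. What the blood count adds**

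Listed samples: basal, -120, -90, -60, -30, 0 (6); 15, 30, 45, 60, 90, 120 (6); 150, 180, 210, 240, 270, 300 (6). The total is 18, and 18 × 8 = 144 mL, as budgeted. If the first-biopsy sample moved to t=-60 it would coincide with the sample already listed there, leaving 17 × 8 = 136 mL. The count therefore rules out the first alternative above. It does not separate a start at -150 from one at -210, because both give 18 samples. The choice of -210 rests on the two durations.

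**5. Check of the corrected clock**

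With the start at t=-210: -210 + 90 = -120 and -210 + 510 = 300. The rest, the biopsy label, the infusion length and the 18 samples all agree. Every time from t=-120 onward is unchanged, including the 120 minutes between the first and second biopsies.

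**The case against.** The strongest reply is that the 8½ h may describe the day rather than the infusion. The end of the infusion is nowhere labelled t=300, and in both places the figure directly follows the words for the test day. If the 8½ h and the 90 minutes both ran from arrival at 8.00 am, arrival would be t=-210, an hour for placing catheters would bring basal blood to t=-150, and the biopsy at t=-120 would be 90 minutes after arrival. Every printed number would then fit, and moving the basal sample to t=-210 would put it at the moment of arrival.

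This does not survive the text. Section 6.3.2 places the rest after the infusion has started, and section 5.2.1 ties the 8½ h to the continuous infusion. The 30-versus-90-minute conflict also stands wherever the infusion is taken to end.

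Three narrower points do stand. The blood count alone cannot establish -210. Figure 2, the time schedule, could not be seen and may already carry the right time, although a correct figure would not repair contradictory prose. And staff who follow the written rest rather than the label would obtain the intended equilibration, so harm depends on which instruction they follow.

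**Conclusion.** The concern holds: the test-day clock is wrong as written. The error is 60 minutes, seen twice: 30 minutes against 90 from prime to first biopsy, and 450 minutes against 510 for the infusion. A single change, -150 to -210, removes both.

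The first conflict needs no assumption beyond the order of events in the text. The second takes the end of the test day to be t=300, the last listed procedure.

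The size of any bias in fasted FSR cannot be derived, because the protocol gives no tracer kinetics or precursor data, and none is claimed. FSR and whole-body turnover are secondary endpoints measured on an optional day, both diets share the clock, and the primary endpoints, sample size and randomised comparison are untouched. It should be fixed because it is an operating instruction for an invasive procedure, not because it threatens the main results.

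**What to change.** In Protocol 6.3.2, (Muscle) protein synthesis, change the time of the basal sample, prime and infusion start from t=-150 to t=-210 min, and make sure Figure 2 shows the same time. Stating there that the infusion stops at t=300 would remove the remaining ambiguity about the 8½ h.

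The cost is one corrected number and a check of the figure. There is no extra sample, biopsy, blood volume or procedure, and the stated infusion length does not change.
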